## Abstract

**Background:**

Sixty percent of people have non-functional arms 6 months after stroke. More effective treatments are needed. Cochrane Reviews show low-quality evidence that task-specific training improves upper limb function. Our feasibility trial showed 56 h of task-specific training over 6 weeks resulted in an increase of a median 6 points on the Action Research Arm test (ARAT), demonstrating the need for more definitive evidence from a larger randomised controlled trial. Task-AT Home is a two-arm, assessor-blinded, multicentre randomised, controlled study, conducted in the home setting.

**Aim:**

The objective is to determine whether task-specific training is a more effective treatment than usual care, for improving upper limb function, amount of upper limb use, and health related quality of life at 6 weeks and 6 months after intervention commencement. Our primary hypothesis is that upper limb function will achieve a ≥ 5 point improvement on the ARAT in the task-specific training group compared to the usual care group, after 6 weeks of intervention.

**Methods:**

Participants living at home, with remaining upper limb deficit, are recruited at 3 months after stroke from sites in NSW and Victoria, Australia. Following baseline assessment, participants are randomised to 6 weeks of either task-specific or usual care intervention, stratified for upper limb function based on the ARAT score. The task-specific group receive 14 h of therapist-led task-specific training plus 42 h of guided self-practice. The primary outcome measure is the ARAT at 6 weeks. Secondary measures include the Motor Activity Log (MAL) at 6 weeks and the ARAT, MAL and EQ5D-5 L at 6 months. Assessments occur at baseline, after 6 weeks of intervention, and at 6 months after intervention commencement. Analysis will be intention to treat using a generalised linear mixed model to report estimated mean differences in scores between the two groups at each timepoint with 95% confidence interval and value of *p*.

**Discussion:**

If the task-specific home-based training programme is more effective than usual care in improving arm function, implementation of the programme into clinical practice would potentially lead to improvements in upper limb function and quality of life for people with stroke.

**Clinical Trial Registration:**

ANZCTR.org.au/ACTRN12617001631392p.aspx

## Introduction

### Background and rationale

Worldwide, 12.2 million people had a stroke in 2019 (1). In Australia, where this study occurs, 1,000 new strokes occur every week and the resultant cost burden is $5 billion a year (2). Problems performing everyday activities of daily living persist 6 months after stroke for 95% of people (3), largely due to not being able to use the arm. Only half of all stroke survivors with an initial affected upper limb regain some useful upper limb function after 6 months (4). Sixty percent of severely impaired and 30% moderately impaired stroke survivors have been reported as having non-functional arms after 6 months (5). Poor recovery of upper limb function is associated with a low health-related quality of life (6, 7).

A Cochrane systematic review of repetitive task training in 2007 (8), most recently updated in 2017 (9), showed a moderate level of evidence for effect of task-specific training on functional ambulation and walking distance, but a low level of evidence for effect on arm and hand function, at ≤6 months after stroke. At the time of conceiving this trial, few studies (10, 11) had directly addressed the hypotheses that task-specific training for the upper limb is more effective than usual care. Several exploratory studies had compared task-specific/functional training to other interventions. For example, Winstein et al. (11) compared 22 participants receiving functional training *in addition to current practice* to 21 receiving *only* usual care, and found an advantage for functional training. Other studies compared task-specific training to alternative treatments such as strength training (12), education (13) or Brunnstrom and Bobath technique (14). About half of the existing studies at the time favoured task-specific training but all were small in sample size (*N* < 53), most had design limitations (e.g., lack of intention to treat analysis, blinded assessor, poor allocation concealment) and several combined the treatment with added interventions so the effect of task-specific training alone could not be estimated. Encouragingly, the EXCITE trial of constraint-induced therapy (CIMT), which contains functional training similar to task-specific training and which was community based, found a positive effect for CIMT on the Wolf Motor Function test at 12 months (primary outcome Wolf Motor Function test) (15).

In a phased approach to developing better treatments, in 2014 we completed a Phase II feasibility RCT with 48 participants (24 task-specific, 23 usual care) using an preliminary version of the design in this protocol (16). Proof-of-concept of task-specific training was demonstrated, with an improvement in median ARAT score (primary outcome measure: range 0–57) of the task-specific group from 8.5 (IQR: 3.0, 24.0) at baseline to 14.5 (3.5, 26.0) at 6 months, compared the usual care group, which had a median score of 4 (3.0, 14.0) which did not change (17). Participants, 85% of whom had moderate–severe impairment, performed a median 157 repetitions per visit plus a median 52 repetitions per day of self-practice, fulfilling the goal of 100–300 reps per day, proving the treatment dose is feasible. 96% of participants rated task-specific training acceptable, 71% rated 1 h of independent practice/day acceptable and 83% reported it improved their arm function. There were no serious adverse events. Based on the results of the feasibility study, we decided to go to the next step to conduct a Phase III trial to investigate effectiveness.

Given that a several existing studies show positive effects of task-specific training compared to other interventions, an important pragmatic question to be answered is whether the new treatment is more beneficial than care routinely delivered now. Consequently, we chose as our comparator group, usual care, where we will not alter treatment intensity or content in the usual care group. Usual care may provide less treatment, but intensity between the two groups will not be matched for the following reasons: (1) matching intensity would not be a true comparison to usual care, because current service provision does not currently offer the proposed intensity of treatment; (2) it is known that increasing intensity of current practice does not deliver the quantum change needed to improve stroke outcome at a population level (18). The importance of our question to health service providers overrides the potential for a difference in intensity of the two treatments. Moreover, if task-specific training is shown to be effective, there will be incentive for increasing intensity when implemented. Treatment intensity will however be carefully recorded.

Since the conception of the present study, in 2016 a randomised controlled trial with 361 participants with stroke, comparing task-oriented rehabilitation to dose-equivalent occupational therapy, or to usual care was published by Winstein et al. (ICARE trial) (19). Findings revealed that a structured, task-oriented rehabilitation program did not significantly improve motor function or recovery beyond either an equivalent or a lower dose of usual care upper extremity rehabilitation. The therapy content was 30 h delivered over 10 weeks and consisted of “intense bouts of task-specific practice, strengthening exercises, shoulder stability/mobility training and motivational enhancements to enable self-confidence and autonomy support to use the stroke-affected arm and hand in valued activities outside the clinic” (19) (Supplementary content, etable2). As the ICARE trial had a similar aim to our study, it is of interest to compare the methods. There are some key differences. We have a more intensive 56 h of intervention over 6 weeks, compared to 30 h over 10 weeks in Winstein 2016 (19). Our study is home-based rather than outpatient based. Primary outcome measure and timepoint also differ. Our primary outcome timepoint (ARAT) is immediately after the intervention at 6 weeks and at 6 months post-randomization. In comparison, in the ICARE trial, the primary outcome (log-transformed Wolf Motor Function Test time score) was measured at 12 months post-randomization. Our study will provide key additional information on the effect of intensity, timing of primary outcome measure and environment. In addition, another small trial was also reported in 2019 (20) comparing task-oriented training to usual care, for the upper limb, with 14 participants allocated to each group. The task-oriented group improved significantly more than usual care on the Wolf Motor Function Test and the Fugl-Meyer upper extremity assessment.

There is a trend to moving inpatient rehabilitation services into the community (21). In Australia in 2020 for example, 42% of services were providing early discharge services compared to 17% in 2016 (22). It follows that much upper limb recovery occurs in the community, after discharge from hospital. At the time of conceiving this study however, a Cochrane review of a range of upper-limb therapies at home (23) showed that we did not yet know if therapy was effective in the home. The likelihood is that home-based treatment will be more beneficial than hospital-based treatment since practice in the person’s own environment is more meaningful (24). In addition, participants might prefer treatment in their home. For example, 96% of participants in our feasibility study (16) found it acceptable. The following two systematic reviews report favourable effects for home rehabilitation in general, though they did not focus particularly on the upper limb. Hillier et al. (25) reported a significant effect in favour of home-based rehabilitation in general compared to centre-based rehabilitation at 6 weeks and 3–6 months post-intervention. Similarly Chi et al. (26) found that home-based rehabilitation led to moderate improvements on physical function in home-dwelling patients with a stroke. To summarise, there are compelling reasons to base therapy at home, but more evidence is still needed.

## Study aims and hypotheses

The primary aim of the Task-AT Home study is to determine if a 6-week task-specific home-based training programme for stroke survivors is more effective than usual care in improving upper limb function and amount of arm use.

The hypotheses relating to this aim are as follows:

Upper limb function will achieve a ≥ 5 point improvement on the Action Research Arm Test in the task-specific training group compared to the usual care group, immediately after 6 weeks of intervention (primary outcome).Amount of upper limb use in everyday life will achieve a ≥ 1 point improvement on the Motor Activity Log in the task-specific training group compared to the usual care group immediately after 6 weeks of intervention (secondary outcome).The difference in upper limb function on the Action Research Arm Test between groups will persist to the end of follow up at 6 months after intervention commencement (secondary outcome).

There are 2 secondary aims:

Secondary aim 1: To determine if a 6-week task-specific home-based training programme for stroke survivors is more effective than usual care in improving health related quality of life.Hypothesis for secondary aim 1: Health related quality of life will achieve a minimally important change of 0.08 point improvement on the EQ5D-5 L in the task-specific training group compared to the usual care group at follow up at 6 months.Secondary aim 2: To identify costs and consequences of both interventions, where consequence is measured by change in health related quality of life.

Supplementary aims:

Identify potential barriers and possible solutions to implementation of task-specific training. A qualitative study is being conducted using a narrative inquiry methodology. In-depth interviews with eight stroke survivors, three caregivers and four therapists will capture a broad range of perspectives following participation in the training. A detailed description of this study will be reported elsewhere.Originally a sub-study was included in our plan to determine changes in motor control in response to training, using kinematics of reach-to-grasp., in the task-specific training group compared to the usual care group. However, due to adjustments that needed to be made to recruitment and funding due to Covid-19, resources were instead redirected to execution of the main trial, so this sub-study could not occur.

## Methods and analysis

### Trial design

This study is a two-arm, assessor-blinded, multicentre randomised controlled trial comparing task-specific treatment to usual care for the arm and hand after stroke. The study will occur in participants’ homes with the interventions delivered by therapists upskilled and employed to deliver the task specific research intervention.

Research personnel responsible for data collection will be blinded to the treatment group to which a participant is assigned. Those involved in the delivery of the treatment will not be blinded. We have also aimed to blind participants as much as possible to group allocation by (a) not informing them deliberately of group allocation – instead they were told they would be visited by a therapist soon and the approximate timeline of this visit. The visit would occur within a week of assessment (if allocated to the task-specific treatment) or in approximately 6 weeks (if allocated to usual care).

The trial is registered with the ANZCTR. Appendix 1 shows key Trial Registration data.

### Study population

Participants with stroke affecting upper limb function will represent the target study population. Participants will be identified during their inpatient stay in stroke wards at hospitals, or *via* community stroke services, in New South Wales (NSW) and Victoria, Australia. In NSW these sites include the Local Health Districts of Hunter New England Health (Kurri Kurri, Maitland, Cessnock and Manning Hospitals, Transitional Aged Care Programme Hunter Valley), Central Coast (Gosford, Long Jetty and Wyong Hospitals, Woy Woy Rehabilitation Centre), Mid North Coast (Port Macquarie, Kempsey and Wauchope Hospitals), Berkley Vale Private Hospital and Mt. Wilga Private Rehabilitation Hospital. In Victoria the sites include health services from Austin Health, Eastern Health and Western Health. Potential participants are identified by therapists working in these organisations and are then screened by the trial manager, at between 2.5 and 3.5 months after stroke. Potential participants who learn about the study *via* social media or the Hunter Medical Research Institute (HMRI) website or study website are also able to self-refer to the study by contacting the research team directly.

Inclusion criteria are diagnosis of primary or recurrent stroke, including stroke caused by focal cerebral infarction (ischemic stroke), intracerebral haemorrhage, subarachnoid haemorrhage and cerebral venous thrombosis (27); discharged home (i.e., permanent address, may include care home/sheltered accommodation); approximately 3 months post stroke (between 2.5 and 3.5 months post stroke); remaining upper limb movement deficit defined as being unable to pick up a 6 mm ball bearing from the tabletop, between index finger and thumb, and place it on a shelf 37 cm above table (item from Action Research Arm Test); informed written consent. Exclusion criteria are upper limb movement deficits attributable to non-stroke pathology; unable to lift hand off lap at all when asked to place hand behind head; severe fixed contractures of elbow or wrist (i.e., grade 4 on the modified Ashworth scale).

### Trial interventions

#### Task-specific intervention

The task-specific intervention will be guided by a detailed protocol (28). The intervention will occur in the participant’s home. In brief, the intervention therapist analyses the whole of the task which is to be trained, e.g., reach-to-grasp., to identify movement components to be prioritised for training and individual movement performance targets to be reached. This will be necessarily different for each participant. The person’s visual attention is directed to regulatory cues in the environment, which are organised to be functionally relevant, individualised and varied, by providing meaningful everyday objects of different sizes, weight and shape, in different positions. The therapist’s role is like a sports coach. He/she uses knowledge of critical biomechanical characteristics of the task to give instructions (by demonstration or verbally) which are concrete and task oriented. Repetitive practice and motor learning principles are used to empower the participant to practice on their own.

Training will be delivered according to an exercise manual containing 142 exercises in words and photographs including variations of the exercises to allow for different levels of difficulty and complexity.

The manual was developed during our previous feasibility trial by a team of therapists during the feasibility trial ([name], [name], [name], [name]) (28) with consultation with user representatives and local specialist neurophysiotherapists. It describes the underlying principles, clinical objectives and individual exercises to achieve the stated objectives. It also details a menu of the treatment strategies (in words and pictures) and includes variations of the treatment strategies to allow for different levels of difficulty and complexity. A description of the development of the manual is available (28), however the manual itself is under embargo until the completion of the trial.

Participants receive 14 × 1-h visits from a therapist over the 6 weeks (3 visits in weeks 1–3, 2 visits in weeks 4–5, 1 visit during week 6). This will *replace* any usual care training for the upper limb. The intensity of practice within each 1-h session will be dependent on individual participant’s capabilities, but high numbers of repetitions will be encouraged, with the aim of delivering between 100 and 300 repetitions within each 1-h session. Beyond the target of 100–300 reps, participants will do as many repetitions as they can accomplish in 1 h, within limits of fatigue. Any repetition is counted, full range is not required, and repetitions are recorded on a task-specific therapy log form. The number of minutes spent practising each exercise is also recorded on the form, as well as the number of the session (out of 14 sessions), and the total duration of task-specific practice in each session (minutes).

Stretches may be indicated when decreased muscle length is present as a secondary consequence from having had a stroke. When decreased muscle length is interfering with performance of exercises from the task-specific exercise manual, a maximum of 5 min during the 1-h treatment may be spent in stretching and may include short duration stretches of between 8 s to 5 min. Longer duration stretches, of 20–30 min duration, may also be prescribed as part of the patient’s self-managed programme, to be performed outside of their 1 h daily self-practice. Long duration stretches will not be used in the one-to-one treatment sessions with the therapist. The stretches that may be used are described with photographs in a document ‘Upper Limb Stretches’, which is given to the therapists.

##### Self-practice

Participants will be asked to perform in addition to therapy sessions, 1 h/day of self-practice. Adherence is encouraged by joint goal setting, providing a booklet about recovery from stroke emphasising potential for ‘rewiring’ the brain through practice, and using a self-practice log to record repetitions, and the date on which they were performed. The self-practice log is checked by the therapist at the beginning of each therapy session, and the participant is assisted to record the repetitions done if needed. The role of the carer will be to encourage the participant to practice and assist with equipment to enable practice and with recording practice.

##### Usual care intervention

The control group for this trial will receive ‘usual care’. Usual care will be provided according to the usual provision in the Local health District(s)/health services, by the usual staff (not staff employed on the trial). In usual care the frequency and content of therapy is variable according to the individual’s pathway and the range of community services available. Community rehabilitation services may be delivered *via* early supported discharge, day hospital, community-based rehabilitation provided in the home or outpatient rehabilitation (29). Usual care variously consists of facilitation of muscle activity, strengthening exercises, soft tissue and joint mobilisation, positioning, training of sensation, and education (30). While it may include practice of everyday functions, it does not include systematic practice of part-tasks, biomechanical analysis, engaging environmental cues or high numbers of repetitions. Usual care therapists will be requested to indicate any treatment they used for an identified participant on a checklist form listing usual care treatment activities called the Upper Limb Usual Care Therapy Log.

Participants allocated to the usual care group will be provided with a booklet about recovery after stroke, with information about details of the frequency of assessment visits rather than about task-specific training. At the end of a participant’s involvement in the trial, at 6 months after recruitment, the usual care participants will be offered a one-off consultation with a research therapist, in which several exercises from the task-specific manual will be recommended.

### Who delivers treatment, amount of treatment and adherence

Different therapists will deliver the usual care and task-specific interventions. Usual care will be delivered by the usual clinical service physiotherapists and/or occupational therapists. Task-specific intervention will be delivered by a group of therapists employed to deliver the intervention in the trial. Intervention therapists will be trained to deliver task-specific training over a 2-day course including theory, and practice with participants with stroke, prior to delivering the treatment. Further training sessions with participants with stroke, and/or follow-up discussion about intervention, with the trainer are available, if needed. Therapists will also receive instruction in the importance of strictly following the treatment manual.

The treatment duration for the task-specific intervention will be 6 weeks, with 1-h visits occurring 3 times in the first 3 weeks, twice in each of the next 2 weeks, then once in the final week, (tapered to increase self-management).

For each intervention therapist, fidelity to treatment protocol will be assessed. For each therapist, we will aim to assess fidelity on 4 separate occasions. A treatment fidelity checklist will be used. If fidelity to treatment schedule is <90% then further training will be given within the 2 weeks following the fidelity assessment, until the 90% criteria is achieved.

### Outcomes

All outcome measures are performed immediately after the 6 weeks of intervention and at 6 months after intervention commencement by an assessor blind to group allocation. The primary outcome measure is a test of arm function and impairment, the Action Research Arm Test (ARAT) (31), immediately after the 6 weeks of intervention. It consists of 19 items focusing on grasping objects of different shapes and sizes, and gross arm movements. Each item is given an ordinal score of 0, 1, 2, or 3 with higher values indicating better function. The test has high inter-rater and test–retest reliability, good validity and is sensitive to therapy-related changes after stroke. A standardized test protocol will be followed (32).

Secondary outcome measures are (a) the Motor Activity Log (33); (b) the ARAT at 6 months to indicate whether changes occurring at end of 6 weeks are sustained in the longer term; and (c) the EQ5D-5 L (34). The Motor Activity Log is a self-report of quality of upper limb movement and amount of use, to capture the patient perspective. A clinically important mean change on the Motor Activity Log is ≥1; (scale range 0–5). This is a valid, reliable and responsive tool and its scores are strongly correlated with arm accelerometry data (33). The EQ5D-5 L is a standardised measure of health status providing a simple, generic measure of health for clinical and economic appraisal (34). It includes a descriptive system comprising 5 dimensions - mobility, self-care, usual activities, pain/discomfort, and anxiety/depression. Each dimension has 5 levels: no problems, slight problems, moderate problems, severe problems, and extreme problems. It also includes a Visual Analogue scale which records the respondent’s self-rated health on a 20 cm vertical, visual analogue scale with endpoints labelled ‘the best health you can imagine’ and ‘the worst health you can imagine’.

Tertiary outcomes are (a) the Wolf Motor Function test (WMFT) (35); (b) the Fugl-Meyer assessment (upper limb section) (36); (c) the Caregiver Strain Index; and (d) the modified Rankin Scale. The Wolf Motor Function Test assesses a wide range of functional abilities of the upper limb. Fifteen movements both with and without objects are measured according to quality of task performance (graded 0–5) and the time to complete the task. In addition, the number of tasks that can be performed in less than 120 s is assessed. The test is responsive to measuring changes in our target group (15), has high inter-rater reliability, test–retest reliability, internal consistency, and construct validity (35, 37).

The upper limb section of the Fugl-Meyer assessment (FM-UL) (36, 38) is also included as this assessment has been identified by consensus at the Stroke Recovery and Rehabilitation Roundtable (39) as a core measure of sensorimotor recovery that should be included in stroke trials, to allow future pooling of participant data across studies and institutions aiding meta-analyses of completed trials. Caregiver burden will be assessed using the Caregiver Strain Index (40). The CSI is included as we would expect carer burden to decrease with improved upper limb function. The Modified Rankin Scale will be used to measure degree of disability or dependence (41). Finally, to allow determination of costs associated with treatments, the Client Services Receipt Inventory will be used (42).

The time schedule of enrolment, interventions and assessments, is shown in Figure 1.

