### Protocol amendments

The protocol was updated twice following trial registration. Both updates occurred after enrolment was initiated on 12/12/2018 as outlined below.

Post-enrolment revision #1 (randomized accrual at this time = 12): The first revision was made 27/08/20.

New recruitment sites Berkley Vale Private Hospital and Mt. Wilga Private Rehabilitation Hospital were added. Outcome measures were added: the Stroke Self-Efficacy Questionnaire, Sheffield Screening Test Receptive Skills, Stroke Aphasic Depression Questionnaire and Hospital Anxiety and Depression Scale. A stretching document was produced to guide the use of stretches during the task specific visits. An ‘Upper Limb Usual Care Therapy Log’ form was developed for treatment of participants allocated to receive usual care. A column for ‘time’ was added to the Therapist’s ‘Task Specific Therapy Log’ form for each task specific exercise. Extra clarification of surrounding time between baseline and task specific therapy, with task specific therapy starting 1 week after baseline, and that participant assessments should occur within 3 days either side of an appointment which is cancelled. A document describing the assessment of fidelity to treatment intervention was developed. Adjustments to assessment and therapy procedures for Covid19 were added.

Post-enrolment revision #2 (randomized accrual at this time = 31). The second revision was made 15/09/21.

New recruitment sites, the Central Coast Local Health District and the Mid North Coast Local Health District of NSW, and Eastern Health and Western Health, in Victoria. Further advice re COVID-19 Vaccination will be mandatory for all NSW staff with first vaccination was added.

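### Outcome visits are anchored to an intervention start that usual care does not have, so the primary assessment can fall about 0 to 1 week later after baseline in the task-specific arm

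*Protocol article*

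**What the plan says.** The Outcomes section fixes the schedule for every measure, including the primary one: "All outcome measures are performed immediately after the 6 weeks of intervention and at 6 months after intervention commencement". The Abstract, Study aims and hypotheses, and Statistical analysis sections use the same two reference points.

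For the task-specific arm the reference points exist. Trial design puts the first therapy visit at most a week after the baseline assessment. The summary of the first revision under Protocol amendments describes it as "with task specific therapy starting 1 week after baseline". The section on who delivers treatment adds: "The treatment duration for the task-specific intervention will be 6 weeks". Under Changes to therapy procedures, sessions missed because of a Covid-related pause may be added, up to 8 weeks from the first session.

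For usual care there is no such date. The Usual care intervention section describes existing services, given by non-trial staff, that vary with the individual's pathway. Trial design says the next visit comes "or in approximately 6 weeks (if allocated to usual care", and Participant recruitment says that these participants are phoned about the date of their next assessment.

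Two other places use different anchors. Background and rationale says: "Our primary outcome timepoint (ARAT) is immediately after the intervention at 6 weeks and at 6 months post-randomization". The Usual care intervention section says: "at 6 months after recruitment, the usual care participants will be offered a one-off consultation with a research therapist".

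**The concern.** A randomised comparison needs outcomes measured at the same time since randomisation in both arms. Here the reference date is an event that only one arm experiences. If the text is followed literally, the task-specific visit moves with the start and end of therapy, while the usual care visit is set by some other, unstated rule.

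Participants enter 2.5 to 3.5 months after stroke. If arm function is still improving by itself at that stage, a later assessment adds recovery to one arm only, in the direction that favours the intervention, and it does so in the primary comparison. The model described under Statistical analysis has terms for group, time and their interaction, and does not mention the actual assessment date, so nothing stated there would remove the difference.

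Separately, the 6-month point carries three anchors (commencement, randomisation, recruitment), and one sentence in Background and rationale lists 6 months as part of the primary timepoint. These passages conflict whatever the size of any bias.

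**Working it through.** The article states no figure for the difference in timing between arms, so there is none to reproduce. The gap has to be built from the stated intervals.

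**Step 1: timing of the primary assessment.** Inputs:
- Start lag after baseline, task-specific arm: 0 to 1 week (Trial design), or 1 week (Protocol amendments).
- Treatment duration: 6 weeks (section on who delivers treatment), or up to 8 weeks from the first session after a Covid-related pause (Changes to therapy procedures).
- Next visit in usual care: about 6 weeks after baseline (Trial design). It is taken to be the outcome visit because Participant recruitment names an assessment as the next contact for this arm.

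Formula: gap = (start lag + treatment duration) − 6 weeks.

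| Start lag (weeks) | Duration (weeks) | Task-specific visit (weeks after baseline) | Gap (weeks) |
|---|---|---|---|
| 0 | 6 | 6 | 0 |
| 1 | 6 | 7 | 1 |
| 0 | 8 | 8 | 2 |
| 1 | 8 | 9 | 3 |

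The last two rows apply only to participants who use the whole extension, and only if the visit waits for therapy to finish.

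**Step 2: timing of the 6-month assessment.** Counted from commencement in one arm and from baseline or randomisation in the other, the gap equals the start lag, 0 to 1 week. The extension does not move it.

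**Step 3: size of the bias for an uninterrupted course.** The article gives no weekly recovery rate. Assume 0.1 to 0.5 ARAT points per week. Bias b = rate × gap, so a 1-week gap gives 0.1 to 0.5 points. Against the 5-point target this is 0.1/5 = 2% to 0.5/5 = 10%.

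**Step 4: effect on the two-sided error.** Sample size gives SD 18 and a baseline to follow-up correlation of 0.72.
- SD after baseline adjustment: 18 × √(1 − 0.72²) = 12.49.
- Standard error: SE = 12.49 × √(2/n), with n analysed per arm.
- n = 120 (150 less 20%): SE = 1.61.
- n = 40 (half of the revised 100 in Modifications due to Covid-19, less 20%): SE = 2.79.
- Error rate: 1 − Φ(1.96 − b/SE) + Φ(−1.96 − b/SE).

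| n per arm | b = 0.1 | b = 0.5 |
|---|---|---|
| 120 | 0.050 | 0.061 |
| 40 | 0.050 | 0.054 |

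With a recovery rate of 0, b = 0 and the error stays at 0.050.

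**The case against.** The strongest reply is that no usual care visit schedule is stated at all. The figure of about 6 weeks comes from a paragraph on blinding that reports what participants are told, and it speaks of a therapist's visit. It is approximate and could absorb some of the start lag. Figure 1, which holds the time schedule, is not shown, and the full protocol may align the visits. Changes to assessment procedures also lets assessments be postponed for Covid reasons in either arm, so control visits can slip too. All of this stands as a limit on the size of the gap. None of it gives the control arm a defined zero or reconciles the three anchors.

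A reader might infer a gap of 1 to 3 weeks for the arm as a whole. The documents do not support that. The ordinary range starts at 0, and the upper end needs a full Covid extension. The extension rule adds sessions after the 6-week period without saying that the assessment moves. Multiplying 3 weeks by the top assumed rate gives 1.5 points, and with 120 analysed per arm an error near 15%. That requires every task-specific participant to have the longest gap, and a sample that the article no longer expects.

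A reader might also infer that the usual care consultation could come before the final assessment. The Usual care intervention section places it at the end of involvement, and Data management defines that end as completing the 6-month follow-up, so it follows the assessment. Only the anchor is mismatched.

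Finally, the feasibility trial's usual care median did not change, which points to little background recovery. That is fair evidence for a bias near 0, although an unchanged median does not exclude a change in the mean.

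**Conclusion.** The point holds in a limited form. The anchor for both outcome visits is undefined in usual care, the 6-month point has three different anchors, and the stated intervals put the task-specific primary assessment about 0 to 1 week later after baseline. The direction favours the intervention if recovery continues.

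The likely size is small: up to 0.5 points and an error of at most about 6% for an uninterrupted course, and close to nothing if usual care is flat. This rests on an assumed recovery rate and on reading the 6-week contact in usual care as the outcome visit. The listing of 6 months as a primary timepoint is a slip in the introduction; every other section makes 6 weeks the sole primary timepoint. The issue still deserves correction because it is systematic, bears on the primary comparison and is cheap to remove.

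**What to change.** - Time both outcome visits in both arms from randomisation, a date every participant has, with the same target and window. Set the primary target late enough to cover the permitted start delay plus the treatment period: 1 + 6 = 7 weeks.
- State whether the primary visit moves when sessions are added after a Covid-related pause.
- Bring Background and rationale, Trial design, Usual care intervention, Outcomes, Changes to therapy procedures and Protocol amendments into line with that anchor, and remove 6 months as a primary timepoint from Background and rationale.
- For participants already assessed, report days from randomisation to assessment by arm, and add a sensitivity analysis of the primary outcome that accounts for actual assessment time.

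The cost is a visit-window amendment and some rescheduling; the last step needs only the randomisation and assessment dates. There are two drawbacks. A few participants with paused therapy may be assessed before their added sessions, which slightly changes the post-treatment question for them. Retiming during the trial also mixes two schedules, which is a further reason to report actual days by arm.
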